### MIG Intervention

Two trained personnel will deliver MIG sessions (Figure 
1).The interview will be conducted in a quiet room within the clinic, in the participant’s preferred language (Hausa or English). Interviewers and participants will be asked to switch off their mobile phones. The participant may be accompanied by someone of their choice.

**Figure 1 F1:**
[figure not shown]
**Randomization Flow chart.** IOP, intraocular pressure; MIG, motivational interviewing modified for glaucoma.

The interviewers will introduce themselves and explain that the session will be confidential. The interviewer will then try to engage the participant by presenting an agenda for discussion, giving the participant the option to choose where to start. The topics covered will be: awareness of glaucoma and the consequences of no treatment; acceptance of treatment options, especially surgery; adherence to topical medication when prescribed; and need for follow up to monitor the pressure inside the eye.

Open-ended questions will be used, with active listening and reflections. The interviewer will seek to understand the participant’s perspective in an empathic fashion. Participant autonomy will be honored as information on glaucoma and its treatment will only be given if requested, or after gaining permission if the participant seems ready for this. The interviewer will listen for change talk, such as participants showing desire for surgery with terms like ‘I wish to’; or an ability to undergo surgery, with ‘I can’; or a reason for change, such as ‘I need vision to save my job’; or commitment, with terms like ‘I intend to’; or even a statement showing that the participant is already taking steps to come for surgery, ‘I have discussed the need for financial support with my family’. The interviewer responds appropriately with reflections, affirmations, and requests for further elaboration or further evocation. At the end of the session, a summary of the interview will be presented to the participant by the interviewer.

The MIG sessions will seek to follow the spirit of MI, and will be recorded for later fidelity testing. Each interview session will last 30 to 60 minutes. All interview records will be kept in a locked cabinet in the office. After the interview, the WAI Short Questionnaire will be administered to establish if there was rapport and to assess the interviewer and patient’s thoughts about the interview.

Under some circumstances a second MIG session might be required if the participant could not stay for the session on the day of recruitment, if the interview was not completed as the participant had to leave, or if there were frequent interruptions from the companion or others. If, in the opinion of the interviewer, the session could not be conducted as planned, the reasons will be recorded and the participant offered a second session.

### Assessing the quality of the MIG intervention

This will be undertaken in three ways. Firstly, the WAI Short Questionnaire, which is completed by the interviewer and participant immediately after the session, will be used to investigate the relationship between the perceived quality of the interview and trial outcomes (Additional files
3 and
4). Participants who cannot see well, or who cannot read the questionnaire themselves will have the questions read out to them by the other interviewer (to reduce bias). Secondly, a random sample of interviews in English, and translated interview transcripts in Hausa will be sent for independent fidelity testing using the MITI scale, a validated tool used for fidelity testing of MI. Thirdly, taped interviews in Hausa and English will be listened to by [name] and the interviewers on a regular basis throughout the trial as part of supervision sessions, to discuss how well the sessions are going, to identify issues which arise and learning needs, and how interviewing could be improved.

### Outcomes

#### Primary outcome

The primary outcome will be the proportion of participants undergoing laser treatment or surgery within two months of the date given to attend the hospital for the procedure (Table 
2. Participant timeline).

**Table 2 T2:** Participants time line

**Participant timeline:**				
	**T0**	**T1**	**T2**	**T3**
		**Date for surgery/laser + 2 months**	**T0 + 6 months**	**T0 + 12 months**
Diagnosis of glaucoma	X			
Standard explanation of disease/treatment	X			
Prescribed eye drops	X			
Recruitment	X			
Randomization	X			
MIG session	Yes/No			
**Primary outcome assessment:**				
Attended for surgery/laser		Yes/No		
**Secondary outcome assessment:**				
Visual acuity and IOP			X	X
**Other measures:**				
Adherence to topical medication			X	X
Reasons for not undergoing procedure			X	

#### Secondary outcomes

At 6 and 12 months after randomization the following will be assessed and recorded: mean IOP (can be measured by Tonopen in their home, if needed); proportion with loss of three of more lines of visual acuity, or loss of form vision (cannot read any letters on the chart) measured using a LogMar chart. This can be measured in their home, if needed; and mean number of follow-up visits to monitor IOP and other clinical parameters.

### Other data

At 6 months from the date given for laser treatment or surgery, a subset of participants in each arm of the trial who do not undergo laser treatment or surgery will be contacted and asked to return to the clinic. Those who attend will be re-offered treatment; those who do not attend will be visited in their homes. The following data will be collected from all: scores using the Morisky questionnaire to assess adherence to topical medication, and reasons why participants did not undergo surgery or laser in both arms of the trial.

### Sample size calculation

The sample size is based on the primary outcome and calculated using the SAMPSI command in Stata 12.1 statistical software (StataCorp Texas, USA). Based on the pilot study, we anticipate that 35% of participants in the standard care group will undergo surgery or laser within two months of the date given for the procedure. A sample size of 150 in each arm will be required to detect an acceptance rate of 52.5% (50% relative and 17.5% absolute increase in acceptance) in people in the intervention arm (power 0.8, alpha 0.05). This is based on a calculation of 137 in each arm rounded up to 150 in each arm to allow for loss to follow-up. We believe this absolute increase of 17.5% (corresponding to a relative increase of 50% assuming a 35% acceptance in the control group) would be an important effect to detect. We have also calculated the power of a study of this size to detect differences between the treatment groups with respect to the secondary outcomes. IOP at entry to the study will average approximately 35 mmHg (SD +/- 14 mmHg) (values resulting from the pilot study). Our outcome is based on the final IOP at 12 months. This is likely to be in the order of 25 mmHg in the standard care group. The study will have good power (0.84) to detect differences of 5mmHG or more between the two groups at one year.

We have less information on the probability of losing three or more lines of visual acuity over the year. Figure 
2 shows the proportion of participants losing three or more lines of visual acuity in the standard care group, with power curves for risk ratios of 0.5 and 0.8. It is more likely that we will be able to detect risk ratios in the order of 0.5. The power of the study to detect significant differences using a relative risk of 0.5 is shown in Table 
3.

**Figure 2 F2:**
[figure not shown]
**Proportion of participants losing three or more lines of visual acuity in the standard care group.** RR, Relative risk.

**Table 3 T3:** Power of the study to detect significant differences using a relative risk of 0.5

**% in standard care group losing 3 or more lines of visual acuity over 12 months**	**Power to detect RR of 0.5**
10%	0.35
20%	0.58
30%	0.81
40%	0.94
50%	0.99
60%	1
70%	1
80%	1
90%	1

RR, Relative risk.

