## Methods/Design

The primary hypothesis is that MI, locally adapted for glaucoma and its treatment (MIG), increases the uptake of treatment amongst individuals with advanced glaucoma in Bauchi State, Nigeria.

A randomized controlled trial with 1:1 allocation to intervention or no intervention will be used to test this hypothesis.

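### Table 3, first row: the stated power of 0.35 at 10% control risk does not follow from the method that gives every other row, which yields 0.27

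*Protocol article*

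**What the plan says.** The Sample size calculation section says that the primary-outcome size was "calculated using the SAMPSI command in Stata 12.1 statistical software", with "power 0.8, alpha 0.05", for 35% v 52.5% uptake. On how the recruitment figure arose it says: "This is based on a calculation of 137 in each arm rounded up to 150 in each arm to allow for loss to follow-up".

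The section then turns to the secondary outcomes. For visual acuity it admits that little is known about the control risk, and it refers to Figure 2 and to Table 3, "Power of the study to detect significant differences using a relative risk of 0.5". Table 3 lists powers of 0.35, 0.58, 0.81, 0.94 and 0.99 for standard care risks of 10%, 20%, 30%, 40% and 50%, and 1 for risks of 60% to 90%. No row is marked as using a different formula or a different number of participants.

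**The concern.** Rows of one power table should come from one formula and one sample size. The table does not state either, but its entries and the other powers in the article are enough to identify both. Once they are identified, the first row stands apart.

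The stake is modest but real. Visual acuity loss is a named secondary outcome. Because the control risk is acknowledged to be poorly known, Table 3 is the reader's numerical guide to what the trial can show at each plausible risk. The discrepant cell lies where the trial is weakest, and the error is in the optimistic direction.

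**Working it through.** **Inputs**
- Alpha 0.05, taken as two-sided (the article does not state sidedness): z = 1.96.
- 137 per arm before the allowance for loss, 150 per arm recruited (Sample size calculation).
- 1:1 allocation (Methods/Design).
- Table 3: control risk p1, intervention risk p2 = p1/2.

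**Step 1. Identify the method from the primary sample size.** For 0.35 v 0.525 the mean proportion is 0.4375 and the difference d is 0.175.

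Uncorrected: n0 = [1.96·√(2·0.4375·0.5625) + 0.8416·√(0.35·0.65 + 0.525·0.475)]² / 0.175² = 124.96, so 125.

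With continuity correction: n = (n0/4)·[1 + √(1 + 4/(n0·d))]² = 136.1, so 137.

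The stated 137 is the corrected figure.

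**Step 2. Power formula.** With p̄ = (p1 + p2)/2:
- se0 = √(2·p̄(1 − p̄)/n)
- se1 = √([p1(1 − p1) + p2(1 − p2)]/n)
- corrected power = Φ[(d − 1/n − 1.96·se0)/se1]
- uncorrected power: the same without 1/n

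**Step 3. Check the method and n on other stated powers.** At n = 137 with correction, the Discussion's three scenarios give:
- 30% v 45%: 0.686 (stated 0.69)
- 30% v 48%: 0.838 (stated 0.84)
- 40% v 60%: 0.895 (stated 0.90)

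The IOP power confirms n = 137 separately. With SD 14 and a difference of 5, the standard error is 14·√(2/137) = 1.692, and Φ(5/1.692 − 1.96) = 0.840 (stated 0.84). At 150 per arm it would be 0.871.

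**Step 4. Table 3.**

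| Control v intervention risk | Stated | Corrected, n = 137 | Uncorrected, n = 137 |
|---|---|---|---|
| 10% v 5% | 0.35 | **0.267** | 0.348 |
| 20% v 10% | 0.58 | 0.576 | 0.641 |
| 30% v 15% | 0.81 | 0.811 | 0.848 |
| 40% v 20% | 0.94 | 0.940 | 0.955 |
| 50% v 25% | 0.99 | 0.988 | 0.992 |
| 60% v 30% | 1 | 0.999 | 0.999 |
| 70% to 90% | 1 | 1.000 | 1.000 |

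First row in full: se0 = 0.03182 and se1 = 0.03168. Corrected: (0.05 − 0.00730 − 1.96·0.03182)/0.03168 = −0.62, and Φ(−0.62) = 0.27. Uncorrected: (0.05 − 1.96·0.03182)/0.03168 = −0.39, and Φ(−0.39) = 0.35.

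**Step 5. Look for one reading that fits the whole table.**
- At 150 per arm the first row is 0.295 corrected and 0.375 uncorrected. Neither is 0.35.
- Uncorrected, 0.35 arises only for n of 136 to 140. There the 20% row is 0.64 to 0.65 and the 30% row 0.85 to 0.86.
- Corrected, 0.35 needs n of 174 to 178, more than the trial will recruit. There the 20% row is 0.69 to 0.71.
- Unpooled variance, a Wald test on the log risk ratio, the arcsine formula, one-sided tests and exact tests were also tried. None fits the whole table within two points.
- Fisher's exact test at 137 gives 0.265 for the first row, so the gap is not a failure of the normal approximation at small proportions.

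**The case against.** The strongest reply is that nothing depends on this cell. The sample size rests on the primary outcome, and the visual acuity powers size nothing. The article openly says the control risk is uncertain and never claims that 10% is expected. At 10% the trial is underpowered whether the power is 0.27, 0.30 or 0.35, and the level at which power passes 0.8 (about 30% control risk) does not move. All of this stands, and it is why the point is minor.

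A second reply is that 0.27 is conditional. The article names its software for the primary calculation but states neither the correction nor the number per arm for Table 3. Its text could be read as meaning the recruited 150 per arm, for which the corrected value is 0.295. The method has indeed been inferred by matching. But 150 per arm with the correction would put the 20% and 30% rows at 0.62 and 0.85, which contradicts the printed 0.58 and 0.81, so that reading moves the inconsistency to other rows.

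Third, not every matching row is evidence. Rows from 60% upwards round to 1 under either formula, and the 50% row barely discriminates. The weight is carried by the 20%, 30% and 40% rows and the Discussion's three powers, which is sufficient. Fourth, the cause is unknown: the row may have been run without the correction, or mis-transcribed. The mismatch does not depend on which.

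**Conclusion.** The concern holds. The first row of Table 3 is inconsistent with the rest of the table: stated 0.35, against 0.27 by the method and number per arm that reproduce the other eight rows. The overstatement is 0.35 − 0.267 = 0.083, or 31% of 0.267. Measured against 150 per arm (0.295) it would be 0.055.

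This rests on a two-sided alpha of 0.05 and on the inferred use of a continuity-corrected test at 137 per arm. That the row was computed without the correction is the likeliest explanation (0.348 rounds to 0.35), but it remains an inference. The primary outcome, the recruitment target and the other entries in the table are unaffected.

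**What to change.** Change the 10% entry in Table 3 to 0.27. Add a note that all rows use 137 per arm, two-sided alpha 0.05 and the continuity correction. If a different calculation was intended for that row, state it and give the reason. If the authors prefer to show power at 150 per arm, every row should be recomputed on that basis, not only the first. Figure 2 was not available for this check, so its 10% point on the curve for a risk ratio of 0.5 should be compared with the corrected cell. The cost is one table cell and a footnote, and a slightly less favourable figure for one scenario.

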### Blinding

Only participants allocated to MIG and the interviewers will know who has been allocated to MIG. The project manager and study ophthalmologist, who will be responsible for obtaining and checking data on the primary outcome, will be blinded to the intervention.

### Ascertainment of outcomes

#### Primary outcome

All data on socioeconomic variables, clinical findings and the date given for surgery will be entered into a customized database on the day of recruitment. Software will be used to generate a spreadsheet which will be constantly updated. The spreadsheet will have the patient’s unique ID, name, sex, hospital number, detailed address, contact phone number, the date given for surgery (or the revised date, if relevant), the date the patient came for surgery and the ‘tracing date’ (date two months after the date given for surgery). The spreadsheet will not contain the randomization sequence number to maintain blinding. The software will be programmed to indicate the date two months after the date booked for laser treatment or surgery (or the revised date). This is the ‘tracing date’ when participants will be traced (see below). Every surgery day the spreadsheet will be reviewed to identify participants who should attend for surgery or laser treatment that day. The surgical register will be checked to see who did and who did not attend on the appointed operation day. The data recording form will be completed. The data will be entered into the database so that the spreadsheet can be updated.

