Everyone suspected of having glaucoma will be referred to the ophthalmologist (usually [name], but other ophthalmologists will also be trained to detect those who are eligible) for a detailed routine ophthalmic examination. The ophthalmologist will confirm the diagnosis of POAG and determine the treatment of choice based the clinical findings (severity) and socio-economic factors likely to influence adherence to medical treatment (such as education and distance from the hospital). Long-term eye drops will be recommended for those who live near the hospital, are educated and can afford topical medication. These individuals will not be eligible for recruitment. Surgery or laser treatment will be recommended for those with an advanced stage of the disease where this offers the best hope for preventing blindness. These individuals will be potential participants. The ophthalmologist will then explain the disease, the treatment options, and the purpose of treatment, as is standard of care. Participants will choose whether to have laser treatment or surgery. The ophthalmologist will then prescribe eye drops and explain how they are to be used whilst waiting for surgery or laser treatment. Everyone offered surgery or laser treatment will be given a date within one month to re-attend for the procedure. Their name and hospital registration number will be written in the surgical register. They will then be escorted to the project manager for recruitment. Participants wishing to change their date of treatment will be offered a new date, and the surgical register, data record form and spreadsheet will be updated.

The eligibility of each potential participant will be checked by the project manager. All those eligible will be recruited after obtaining written informed consent. If the patient does not consent, reasons will be sought and recorded. After obtaining consent a unique identifier number will be issued. All those recruited will be given a red ID card which contains their name, hospital number and study ID. They will be required to present this card at the registration desk at every visit.

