### Primary outcome

Our primary outcome is dichotomous (did or did not attend surgery or laser treatment within two months of their scheduled date). Our effect measure will be the risk ratio, that is, we will calculate the proportion of people with this outcome in the intervention group compared to the standard care group. We will report this with 95% confidence intervals. In a trial of 300 people we anticipate that the groups will be fairly well balanced. However, we will also calculate a risk ratio adjusted for factors that may affect uptake of surgery (stage of glaucoma, age, sex, education, and distance from hospital).

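### The two-month window for the primary outcome has no single starting date: it runs from the date given in one place and from a revised date in another, and the date can be changed after randomisation

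*Protocol article*

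**What the plan says.** **Order of events** (Protocol article, Identification of potential participants and recruitment). "Everyone offered surgery or laser treatment will be given a date within one month to re-attend for the procedure". Next, "They will then be escorted to the project manager for recruitment"; consent and randomisation come after that. The first date therefore precedes allocation.

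**Changes of date** (same section). "Participants wishing to change their date of treatment will be offered a new date", and the trial records are then updated.

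**Time origin of the primary outcome:**
- Outcomes, Primary outcome: "the proportion of participants undergoing laser treatment or surgery within two months of the date given to attend the hospital for the procedure". The Abstract and the Sample size calculation use the same origin.
- Data analyses, Primary outcome: "did or did not attend surgery or laser treatment within two months of their scheduled date".
- Ascertainment of outcomes, Primary outcome: "The software will be programmed to indicate the date two months after the date booked for laser treatment or surgery (or the revised date". The same section, when it lists the spreadsheet fields, ties the tracing date to the date given and mentions no revision at that point.
- Table 2 sets T1 at two months after the date for the procedure, whereas T2 and T3 are counted from T0.

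**The event.** The Abstract, the Outcomes section, the Sample size calculation and the T1 data collection section speak of *undergoing* the procedure. Table 2, the register check under Ascertainment of outcomes and the analysis section speak of *attending*.

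**The concern.** Neither the outcome definition nor the analysis section says whether the original or the revised date counts. The only operational rule lets the limit move with the revised date. A change made after randomisation is participant behaviour, and MIG is meant to strengthen commitment to treatment, so it could plausibly alter how often or how far people rebook. Two participants treated equally late could then be scored differently only because one of them had rebooked.

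Blinding of the project manager and ophthalmologist does not remove this. Rebooking starts with participants, who know whether they had a MIG session. At stake is the comparability of follow-up between arms for the only primary outcome.

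**Working it through.** **1. The plan's own figure.** Inputs from the Sample size calculation: 35% v 52.5%, power 0.8, alpha 0.05. Two-sided normal formula with pooled proportion 0.4375:

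n = [1.96·√(2·0.4375·0.5625) + 0.8416·√(0.35·0.65 + 0.525·0.475)]² / 0.175² ≈ 125.

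Continuity correction: n/4·[1 + √(1 + 4/(n·0.175))]² gives 137 per arm, as stated. The choice of anchor date does not enter this calculation.

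**2. Which procedures are affected.** Let D be the original date and d the postponement. The fixed window ends at D + 2 months and the revised one at D + d + 2 months. A procedure by D + 2 counts under both rules; one after D + d + 2 counts under neither. Only those in between are scored differently.

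D is at most about one month after T0, so the fixed window closes by about 1 + 2 = 3 months. Example (assumed): two participants have D at one month, and one of them postpones by one month. Both are treated at 3.5 months. The rebooker's window ends at 4 months, so that procedure counts. The other's ended at 3 months, so that procedure does not.

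**3. Size of the distortion.** Let r be the proportion of an arm that rebooks and q the share of rebookers treated only in the extra time, taken as equal in both arms. The added difference is (r_MIG − r_control)·q. It is zero if rebooking is equal **or** if q = 0.

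The article gives neither r nor q, so the values below are assumptions. Uptake by D + 2 is set at 35% in both arms, with 150 per arm and a two-sided pooled z-test.

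| r, MIG v control | q | Observed uptake | Risk ratio | Chance of rejection |
|---|---|---|---|---|
| any | 0 | 35% v 35% | 1.00 | 5% |
| 10% v 5% | 0.5 | 40.0% v 37.5% | 0.400/0.375 = 1.07 | about 7% |
| 20% v 10% | 0.5 | 45% v 40% | 0.45/0.40 = 1.125 | about 14% |

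Put as extra events in the MIG arm only: 3 (2.0 points) give 6.5% rejection, 5 (3.3 points) give 9.2%, and 8 (5.3 points) give 15.8%. Over a wider assumed range (excess rebooking of 5 to 20 points, q from 0.1 to 0.5) the addition is 0.5 to 10 points, with risk ratio 1.01 to 1.29 and rejection 5.1% to 42%.

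**4. What the pilot can exclude.** It reports no uptake after the date given among 18 acceptors, 9 of them in the MIG arm. One-sided 95% upper limits for the late share are 1 − 0.05^(1/18) = 15% overall and 1 − 0.05^(1/9) = 28% in the MIG arm. The two illustrations need 5/40 = 12.5% and 10/45 = 22% of MIG-arm uptake to fall in the extra time. Both lie below 28%; only the first lies below 15%.

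**5. Attend or undergo.** Suppose 2% to 10% of attenders in both arms were not treated (assumed). Rates of 35% and 52.5% would become between 34.3% and 51.45%, and 31.5% and 47.25%. Continuity-corrected power at 150 per arm would fall from 0.84 to between 0.83 and 0.77.

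**The case against.** The strongest reply is the pilot. All acceptors came on the date given, which is why the window was cut from four months to two. That is the only evidence in the article on late uptake, and it points to a small effect. This stands, with two limits: 18 acceptors are few, and the article does not say whether a revised date counted as the date given.

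Second, the two-month allowance already absorbs most postponements. A reader might infer that unequal rebooking is enough to bias the comparison. It is not: rebooked procedures done within two months of the original date add nothing, and neither do rebookers who are not treated in the extra time.

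Third, a reader might infer that the window can be extended without limit. The article is silent on repeated changes and speaks of one new date. Limits on rebooking are detail that a condensed article may leave to the full protocol, so no unbounded window can be read from it.

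Fourth, if MIG leads more people to rebook and be treated, that is real uptake, and counting from the agreed date could be a deliberate choice of estimand. That is fair, but the article makes no such choice: its definition, analysis and ascertainment texts differ. Under the revised-date rule, an equally late procedure without rebooking goes uncounted.

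Fifth, *attend* and *undergo* are probably used loosely. The definition says undergo, and the T1 section records whether the procedure was done, which one and when. This largely stands.

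**Conclusion.** The time origin of the primary outcome is inconsistent, and the operational version can move with behaviour after randomisation. The arms could therefore be compared over unequal follow-up. Bias requires both that rebooking differs by arm and that some rebookers are treated more than two months after the original date.

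The documents show neither condition, so the size is unknown and every rate above is an assumption. Against the design difference of 17.5 points, the two illustrations add 2.5 and 5 points. The pilot suggests the effect may be small but cannot exclude it. The attend/undergo difference calls only for aligned wording. Severity: moderate.

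**What to change.** 1. Define the primary window for every participant as two months after the original date recorded at recruitment. Use that anchor in the Outcomes, Ascertainment and Data analyses sections and for T1 in Table 2.
2. Keep the original date in its own field when a revised date is entered. The article says records are updated and lists the date given or revised as one spreadsheet item, so it is unclear whether the original survives. Check this for participants already recruited (70 by the end of January 2014).
3. Report the revised-date window as a sensitivity analysis, with the frequency of rebooking by arm.
4. Score the procedure performed, by procedure date, and align Table 2, the register check and the analysis section with the outcome definition and the T1 data collection section.

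The cost is one formula, one data field and some wording, plus notification through the article's own amendment route. The code is broken only after the primary analysis, so the rule can still be settled blind. Rebooking itself and the 150 per arm do not change. The small downside is that a few late rebooked procedures would count only in the sensitivity analysis.
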